## **6. EFFICACY ANALYSES**

All efficacy analyses are exploratory. In MAD cohorts in Part B and C, exploratory analyses will be performed to describe absolute and relative (%) changes from baseline in lipid parameters, including fasting triglycerides, total cholesterol, low-density lipoprotein cholesterol (LDL-C), and high-density lipoprotein cholesterol (HDL-C). Exploratory subgroup analyses may also be conducted to describe changes in fasting triglycerides in subjects with baseline triglycerides  $\geq 100$  mg/dL versus  $< 100$  mg/dL. Similarly, exploratory subgroup analyses may be performed to describe changes from baseline in fasting LDL-C in subjects with baseline LDL-C  $\geq 100$  mg/dL versus  $< 100$  mg/dL.

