### **1.3. Rationale for the Current Study**

This Phase 1 study will evaluate the administration of TLC-2716 in humans for the first time. The objectives of this first-in-human (FIH) study are to evaluate, in a stepwise fashion, the safety, tolerability, PK, and pharmacodynamics (PD) of single- and multiple-ascending doses of TLC-2716. The results from this study, including safety and PD data across the expected therapeutic range of drug exposures planned for future studies, will form the basis for further evaluation of TLC-2716 and dose selection for a subsequent Phase 2 trial in patients with SHTG, FH, and NASH. In the context of evaluating safety, tolerability, PK, and PD, the latter of which includes changes in serum lipids, potentially impacted by diet, this trial will be conducted in an inpatient setting (confined Phase 1 unit), allowing for consistency in diet and timing of sample collections. To remove potential confounding effects of comorbid disease and/or therapies in patients with metabolic disease, healthy subjects will be recruited for this trial. Of note, in multiple-dose cohorts, a subset of subjects with mild to moderately elevated serum TG and/or LDL will be identified, facilitating an early evaluation of potential lipid-lowering effects of TLC-2716 in otherwise healthy individuals.

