### 3.1.2. Part B: Multiple-Ascending Dose [MAD] (Cohorts 6-10)

Part B will evaluate the safety, tolerability, PK, and PD of multiple-ascending doses of oral TLC-2716 or placebo under fed conditions. Part B will proceed in up to 5 dose-escalation cohorts and will be governed by a review of safety, tolerability, and any available and relevant PK and/or PD data, and study-specific stopping criteria. Planned study treatments within each cohort are provided in [Table 3](#).

- Randomized, blinded (sponsor-unblinded), placebo-controlled, multiple-ascending doses of TLC-2716 in healthy subjects. An attempt will be made to enroll at least 3 subjects in each cohort with Screening TG ≥ 150 mg/dL and/or low-density lipoprotein cholesterol (LDL-C) ≥ 130 mg/dL.
- Within each cohort, 10 unique subjects will be randomized 4:1 to receive either blinded TLC-2716 (N = 8) or PTM (N = 2) QD for 14 days.
- Part B (Cohort 6) may be initiated after the evaluation of cumulative safety, tolerability, and any relevant and available PK and/or PD data from all subjects enrolled in Cohort 3 in Part A (up to and including Day 4).

- For Cohorts 7-10, dosing may be initiated after evaluation of cumulative safety, tolerability, and any relevant and available PK and/or PD data from all subjects enrolled in the previous cohort in Part B through Day 14.
- All study drugs in Part B will be administered in the morning following a standard meal.

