#### **3.7.2. Baseline**

Baseline is defined as the last value obtained before the administration of study intervention (TLC-2716 or placebo), unless otherwise stated. For laboratory data, baseline will be Day -1 for all cohorts in Parts A, B, and C. For ECG parameters, baseline will be Day -1 for SAD Cohorts in Parts A and C, and Day -2 for MAD cohorts in Parts B and C.

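### The optional lipid subgroups in SAP 6 are defined by the same Day -1 value from which change is measured, with no placebo contrast specified, so regression to the mean alone would show a fall in the high group and a rise in the low group

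*Combined protocol and SAP*

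**What the plan says.** SAP section 6 states that in the multiple-dose (MAD) cohorts of Parts B and C "exploratory analyses will be performed to describe absolute and relative (%) changes from baseline in lipid parameters", naming fasting triglycerides (TG), total cholesterol, LDL-C and HDL-C. It then adds two optional splits. For TG: "Exploratory subgroup analyses may also be conducted to describe changes in fasting triglycerides in subjects with baseline triglycerides" of at least 100 versus below 100 mg/dL. For LDL-C: "exploratory subgroup analyses may be performed to describe changes from baseline in fasting LDL-C in subjects with baseline LDL-C" of at least 100 versus below 100 mg/dL. It calls all efficacy analyses exploratory.

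SAP section 3.7.2 fixes the reference value: "For laboratory data, baseline will be Day -1 for all cohorts in Parts A, B, and C". Lipids belong to the laboratory panel.

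The protocol takes a separate interest in subjects with raised lipids. Section 1.3 says of the MAD part of the design: "a subset of subjects with mild to moderately elevated serum TG and/or LDL will be identified, facilitating an early evaluation of potential lipid-lowering effects". Section 3.1.2 says "An attempt will be made to enroll at least 3 subjects in each cohort with Screening TG" of at least 150 mg/dL and/or "low-density lipoprotein cholesterol (LDL-C) ≥ 130 mg/dL". That criterion uses the Screening value, not Day -1. On allocation, section 3.1.2 says "10 unique subjects will be randomized 4:1 to receive either blinded TLC-2716 (N = 8) or PTM (N = 2) QD for 14 days".

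Two other passages bear on placebo. Protocol section 8.8 summarises PD biomarkers by cohort and treatment group. SAP section 3.1 treats placebo subjects as one group in each part, in a paragraph that opens with safety. Neither refers to the lipid subgroups.

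**The concern.** A single lipid measurement is partly the subject's usual level and partly that day's deviation. Sorting subjects on the Day -1 value puts an excess of upward deviations in the group at or above 100 mg/dL and an excess of downward deviations in the group below it. The later measurement carries a fresh deviation. Subtracting the Day -1 value therefore gives a fall in the high group and a rise in the low group even if the drug does nothing.

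This matters because the artefact looks like the finding of interest, namely lipid lowering concentrated in subjects whose lipids are higher. Protocol section 1.3 says the study will form the basis for Phase 2 dose selection, including in severe hypertriglyceridemia and familial hypercholesterolemia. A reader of the active-arm subgroup rows alone could not separate drug effect from regression to the mean.

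**Working it through.** **Figure to reproduce.** None. The plan states no lipid variance, effect size or power.

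**Inputs from the documents.** Cut of 100 mg/dL for both lipids (SAP 6); change from Day -1 (SAP 6 and 3.7.2); 8 active and 2 placebo subjects per cohort, with five cohorts in Part B (protocol 3.1.2), so 40 active and 10 placebo.

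**Assumptions, not in the documents.** Log-normal lipids, independent errors at each visit, no drug effect and no time trend. TG: median 100 mg/dL, between-subject log SD b = 0.40, within-subject log SD w = 0.20 (range 0.15 to 0.30). LDL-C: median 115 mg/dL, b = 0.22, w = 0.08.

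**Formula.** Let S = √(b² + w²) and a = ln(100/median)/S. Then 1 − ρ = w²/S², so (1 − ρ)S = w²/S. The expected log change is

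- high group: −(w²/S) × φ(a)/[1 − Φ(a)]
- low group: +(w²/S) × φ(a)/Φ(a)

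**TG, w = 0.20.** S = √0.20 = 0.4472; w²/S = 0.0894; a = 0; φ(0)/0.5 = 0.798. Log change = ∓0.0714, so −6.9% in the high group and +7.4% in the low group. The false contrast is 14.3 points.

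**Over the range of w, and for LDL-C:**

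| Scenario | w²/S | High group | Low group | Contrast (points) |
|---|---|---|---|---|
| TG, w = 0.15 | 0.0527 | −4.1% | +4.3% | 8.4 |
| TG, w = 0.20 | 0.0894 | −6.9% | +7.4% | 14.3 |
| TG, w = 0.30 | 0.1800 | −13.4% | +15.4% | 28.8 |
| TG, median 120, w = 0.20 | 0.0894 | −4.9% | +10.1% | 15.0 |
| LDL-C | 0.0273 | −1.3% | +3.4% | 4.6 |

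**Wider scenarios.** Null simulations of 2 million subjects each applied the protocol's Screening exclusions and weighted the sample so that at least 30% met the enrichment criterion. For TG (geometric mean 92 to 110 mg/dL, log SD 0.40 to 0.73, ρ 0.6 to 0.9) the median change was −2% to −22% in the high group and +3% to +24% in the low group. For LDL-C (mean 110 to 120 mg/dL, SD 25 to 35 mg/dL, ρ 0.7 to 0.9) it was −1% to −5% in the high group. The direction was the same in every scenario.

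**Classifying on Screening instead.** Under the base TG assumptions, grouping on the Screening value and measuring change from Day -1 gives 0% in both groups within simulation error, whether the cut is 100 or 150 mg/dL. Regression from Screening selection is complete before Day -1. This result needs independent errors and no drift between Day -1 and follow-up.

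**Placebo numbers.** If 40% to 60% of subjects fall in the high group, Part B has 10 × 0.4 = 4 to 10 × 0.6 = 6 pooled placebo subjects there. The chance that a single cohort has none is 0.6² = 36% down to 0.4² = 16%.

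**The case against.** The analysis is optional, descriptive and untested, and it touches neither a primary endpoint nor the sample size. The trial is also randomised against placebo. Both arms regress equally, so a placebo-subtracted change within the same baseline subgroup has expectation zero. SAP 3.1 pools placebo by part and protocol 8.8 tabulates PD data by treatment, so a careful reader might be protected in practice. All of this stands, and it limits the weight of the point. It does not remove it, because section 6 does not say that placebo will be shown within the lipid subgroups.

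Three stronger readings are tempting, and the documents do not support them.

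- **That the enrichment, or the mismatch between 150/130 and 100 mg/dL, causes the bias.** It does not. Applying 150 and 130 mg/dL to the Day -1 value would have the same flaw. The 100 mg/dL cut is a defensible choice for group size. No objective or endpoint promises an analysis of the enriched subset.
- **That placebo cannot reveal the artefact.** With exactly 3 enriched subjects in 10 and 2 on placebo, C(7,2)/C(10,2) = 21/45 = 47% of single cohorts would have no enriched placebo subject. That figure is per cohort and concerns the Screening-enriched subset, not the SAP's groups. Across five Part B cohorts it becomes (21/45)^5, about 2%.
- **That Screening classification is a complete cure.** Subjects move from free living to confinement with standardised meals and alcohol restriction. Drift that differs by lipid level would remain after Screening classification; only the placebo contrast handles it.

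**Conclusion.** The concern holds as a minor point. Because one Day -1 value both defines the subgroup and is subtracted, and no within-subgroup placebo contrast is specified, the planned description would show a fall in the high group and a rise in the low group for an inert drug. The direction follows whenever test-retest correlation is below 1. The size depends on variability that the documents do not give: about 8 to 29 points of false contrast for TG at within-subject log SD 0.15 to 0.30, and about −1% versus +3% for LDL-C. The consequence is confined to how an exploratory result may be read; the primary safety and PK endpoints are not affected.

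**What to change.** In SAP section 6, state that if the lipid subgroups are run:

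1. Subjects are classified on the fasting Screening value. The 100 mg/dL cut may stay.
2. Change is computed from Day -1, as now.
3. Pooled placebo subjects from the MAD cohorts are shown in the same subgroup beside active, and any statement about lipid lowering rests on that comparison.

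Optionally, list or describe the subset meeting the protocol's Screening criterion (TG at least 150 and/or LDL-C at least 130 mg/dL), since protocol section 1.3 says why it was sought.

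The cost is SAP wording. Fasting Screening lipids and randomised placebo data are already collected. There are two downsides: the pooled placebo subgroup is small, at about 4 to 6 subjects in the Part B high group, so the contrast will be imprecise; and Screening is a slightly less current measure of lipid status than Day -1.

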## **7. SAFETY**

### **7.1. Adverse Events and Deaths**

#### **7.1.1. Adverse Event Dictionary**

Clinical and laboratory adverse events (AEs) will be coded using the current version of the Medical Dictionary for Regulatory Activities (MedDRA). System organ class (SOC), high-level group term (HLGT), high-level term (HLT), preferred term (PT), and lower-level term (LLT) will be provided in the AE dataset.

#### **7.1.2. Adverse Event Severity**

Adverse events are graded by the investigator as Grade 1, 2, 3, or 4 according to toxicity criteria specified in the protocol. The severity grade of events for which the investigator did not record severity will be categorized as “missing” for tabular summaries and data listings. The missing category will be presented last in the summary presentation.

#### **7.1.3. Relationship of Adverse Events to Study Drug**

Study drug related AEs are those for which the investigator selected “Related” on the AE case report form (CRF) in response to the question regarding relatedness of AE to study drug. Relatedness will always default to the investigator’s choice, not that of the medical monitor, or designee. Events for which the investigator did not record relationship to study drug will be considered related to study drug for summary purposes. However, by-subject data listings will show the relationship as missing as documented on the CRF.

#### **7.1.4. Relationship of Adverse Events to Study Procedure**

Study procedure related AEs are those for which the investigator selected “Yes” on the AE CRF to the question regarding relatedness to protocol mandated procedures. Relatedness will always default to the investigator’s choice, not that of the medical monitor. Events for which the investigator did not record relationships to study procedure will be considered related to study procedure for summary purposes. However, by-subject data listings will show the relationship as missing from that captured on the CRF.

#### **7.1.5. Serious Adverse Events**

Serious adverse events (SAEs) will be identified and captured as SAEs if the AEs met the definition of SAEs that were specified in the study protocol.

#### **7.1.6. Treatment-Emergent Adverse Events**

##### **7.1.6.1. Definition of Treatment Emergent**

Treatment-emergent adverse events (TEAEs) are defined as 1 or both of the following:

- Any AEs with an onset date on or after the study drug start date and no later than 30 days after permanent discontinuation of study drug. If the AE onset date is the same as the date of study drug start date then the AE onset time must be on or after the study drug start time. If the AE onset time is missing when the start dates are the same the AE will be considered treatment emergent.
- Any AEs leading to premature discontinuation of study drug.

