- c 14 (± 2) days after the last dose of the study drug, all subjects will return for an in-clinic follow-up visit.
- d Assessments will be performed within 72 hours of early termination from the study.
- e Vital signs include blood pressure, pulse, respiration rate, and body temperature.
- f Symptom driven physical exams will be performed during confinement as needed, based on reported signs and symptoms, on days in which complete physical examination is not required.
- g Hematology: CBC with differential. Collected in fasting state prior to morning meal.
- h Serum Chemistry: alkaline phosphatase, AST, ALT, GGT, total bilirubin, direct and indirect bilirubin, total protein, albumin, bicarbonate, BUN, calcium, chloride, creatinine, glucose, phosphorous, magnesium, potassium, sodium, uric acid, and amylase (reflex lipase testing is performed in subjects with total amylase > 1.5 X ULN). Collected in fasting state prior to morning meal.
- i Coagulation: INR, PTT. Collected in fasting state prior to morning meal.
- j Lipids: total cholesterol, HDL, LDL, TG. Collected in fasting state prior to morning meal.
- k To be collected in fasting state prior to morning meal and 12 hours post-dose, with exception of 12-lead ECG which is only required 2 hours post-dose.
- l Females of child-bearing potential only (see [Appendix 3](#) for definition).
- m As necessary only for evaluation of post-menopausal state in females of any age with amenorrhea > 12 months at time of Screening (see [Appendix 3](#)).
- n Collected pre-dose (≤ 10 minutes prior to dosing), 0.25, 0.5, 1, 1.5, 2, 2.5, 3, 3.5, 4, 6, 12, 24, 48, and 72 hours post-dose.
- o Collected pre-dose (≤ 10 minutes prior to dosing), and 4 hours post-dose.
- p The optional genomic sample should be collected on Day -1, but may be collected at any time during the study, if necessary.
- q Subjects to be educated on study requirements and restrictions.
- r From the time of obtaining informed consent through the first administration of the study drug, record all SAEs and any non-serious AEs related to protocol required procedures on the AE eCRF. All other untoward medical occurrences observed during the Screening period, including exacerbation or changes in medical history should be documented on the medical history eCRF. See Section 7 Adverse Events and Toxicity Management for additional details.

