#### **7.3.1.1. Adverse Events**

Following initiation of study medication, collect all AEs, regardless of cause or relationship, until 14 days after last administration of study drug and report to the CRF/eCRF database as instructed.

All AEs should be followed up until resolution or until the AE is stable, if possible.

TLC may request that certain AEs be followed beyond the protocol-defined follow-up period.

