## 8.6. Safety Analysis

All safety data collected on or after the date that study drug was first administered up to the date of last dose of study drug plus 14 days will be summarized by treatment group (according to the study drug received) or treatment sequence using the Safety Analysis Set. As appropriate, placebo-treated subjects will be pooled across Parts A, B, and C of the study.

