### **3.4. Visit Windows**

#### **3.4.1. Definition of Predose and Postdose**

The predose value associated with a treatment is defined as the last available value collected prior to the time of the first dose of the treatment (TLC-2716 or placebo) for the planned cohort

on Day -1, which may occur after placebo treatment of all subjects in MAD cohorts in Part B and C on Day -2.

Postdose value associated with a treatment is defined as any value collected after the first dose of that treatment and on or before the date of the last dose of that treatment plus 30 days, or before the time of the first dose of the following treatment, whichever comes earlier.

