## **7.2. Laboratory Evaluations**

Laboratory data collected during the study will be analyzed and summarized using both quantitative and qualitative methods. Summaries of laboratory data will be provided for the Safety Analysis Set and will include data collected up to the last dose of study drug plus 30 days for subjects who have permanently discontinued study drug. The analysis will be based on values reported in conventional units. When values are BLQ, they will be listed as such, and the imputed value will be used for the purpose of calculating summary statistics. Hemolyzed test results will not be included in the analysis, but they will be listed in by-subject laboratory listings.

A by-subject listing for laboratory test results will be provided by subject ID number and visit in chronological order for hematology, serum chemistry, lipids, coagulation, and urinalysis

separately. As appropriate, abnormal values will be flagged in data listings per Common Terminology Criteria for Adverse Events (CTCAE) v5.0 criteria.

No formal statistical testing is planned.

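### Protocol 8.6 ends the safety summaries 14 days after the last dose and the SAP 30 days after, with no stated departure; the 14-day limit excludes on-schedule follow-up visits at 15 to 16 days.

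*Combined protocol and SAP*

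**What the plan says.** **Protocol, analysis.** Section 8.6 applies to all safety data, from the first administration of study drug, "up to the date of last dose of study drug plus 14 days will be summarized by treatment group".

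**Protocol, collection.** Section 7.3.1.1 collects all adverse events, whatever their cause, "until 14 days after last administration of study drug". Section 7.3.1.2 takes serious adverse events and deaths to 30 days after the last dose.

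**Protocol, schedule.** Footnote c of Table 5 states that 14 ± 2 "days after the last dose of the study drug, all subjects will return for an in-clinic follow-up visit". Footnote c of Table 6 and sections 3.5 and 6.8 agree. Laboratory tests, vital signs, ECG, physical examination and review of adverse events are all marked at that visit. The synopsis and section 6.7 also have adverse events followed for the whole study.

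**SAP.** Five places use 30 days:
- 3.4.1 defines postdose values as those collected "on or before the date of the last dose of that treatment plus 30 days" (or before a following treatment, if earlier).
- 7.1.6.1 gives the treatment-emergent rule, "no later than 30 days after permanent discontinuation of study drug".
- 7.2 says that laboratory summaries take data "up to the last dose of study drug plus 30 days".
- 7.2.2 uses the same limit for treatment-emergent laboratory abnormalities.
- 7.2.2.1 uses it for the denominator of the laboratory abnormality tables.

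The SAP introduction says that it is based on protocol Amendment 1. It does not mention that 30 days replaces 14.

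**The concern.** Adverse events, laboratory abnormalities, ECGs, vital signs and physical examinations are primary endpoints (protocol 8.1.2), so the rule that decides which of these data reach the tables should be the same in both documents. It is not, and a programmer cannot follow both.

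The 14-day limit coincides with the nominal follow-up day and ignores the permitted two days after it. A subject seen on schedule at 15 or 16 days would have follow-up results left out of the summaries, while a subject seen at 13 days would have them included. A serious adverse event that starts three weeks after the last dose is treatment-emergent under the SAP and outside the protocol's summaries. Collection of non-serious events is also unclear for the last two days of the visit window.

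**Working it through.** No sample size or test is involved. The check is date arithmetic, with no Day 0 (SAP 3.7.1).

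**Inputs.** Last dose: Day 1 (SAD), Day 14 (MAD). Admission: Day -1 (SAD), Day -2 (MAD). Follow-up: 14 ± 2 days after the last dose. Stated maximum duration after screening: 18 days for Part A, 32 days for Parts B and C (protocol 3.1).

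**Step 1: reproduce the plan's own durations.** Duration = days before Day 1 + latest study day.
- SAD: latest visit = 1 + 14 + 2 = Day 17; duration = 1 + 17 = 18 days.
- MAD: latest visit = 14 + 14 + 2 = Day 30; duration = 2 + 30 = 32 days.

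Both match. The protocol's own duration therefore counts a follow-up visit 16 days after the last dose as on schedule.

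**Step 2: set the windows against the visit.**

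| | SAD | MAD |
|---|---|---|
| Permitted follow-up days | 13 to 17 | 26 to 30 |
| Protocol 8.6 closes (last dose + 14) | Day 15 | Day 28 |
| SAP closes (last dose + 30) | 1 + 30 = Day 31 | 14 + 30 = Day 44 |
| Permitted days outside protocol 8.6 | 16, 17 | 29, 30 |
| Permitted days outside the SAP window | none | none |

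**Step 3: which data change status.**
- Laboratory tests, vital signs and ECGs from a follow-up visit at +15 or +16 days: out under protocol 8.6, in under the SAP.
- Serious adverse events starting at +15 to +30 days: collected under protocol 7.3.1.2, left out of the summaries by 8.6, treatment-emergent under the SAP.
- Non-serious adverse events starting after +14 days: 7.3.1.1 does not require them, the follow-up review may record them, and the SAP would count those recorded. After the follow-up visit there is no routine collection, so the rest of the SAP window is largely empty for these events.

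**Step 4: size.** For one subject whose only event falls in the disputed period, the change in incidence is 1/8 = 12.5 percentage points in an active cohort of 8.

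**The case against.** The best defence is that the SAP specifies the analyses, so only one set of tables is planned and it includes these data. SAP 3.4.2 uses the nominal visit and reports follow-up as a separate visit. Protocol 8.6.3 itself summarises laboratory data at scheduled visits, and follow-up is one. The summaries are descriptive, and individual listings are kept in any case. This lowers the stakes, but it does not remove the conflict: 8.6 covers all safety data, and the SAP replaces its limit without saying so.

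Three stronger readings are tempting, and the documents do not support them.

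- *A reader might infer that an adverse event starting 15 days after the last dose is never recorded.* Tables 5 and 6 schedule adverse event review at the follow-up visit, with no exception for visits at 15 or 16 days, and the synopsis and section 6.7 continue it throughout the study. The accurate statement is that 7.3.1.1 conflicts with these places.
- *A reader might infer that neither window fits the visit schedule.* The SAP window holds every permitted follow-up visit and equals the reporting period for serious adverse events and deaths. Its only weakness is that it runs past the routine collection of non-serious events, which calls for a footnote. The SAP does not label its percentages as 30-day rates.
- *A reader might turn two of five permitted days into 40% of subjects, or 60 of 150.* That assumes visits spread evenly over the window, which nothing in the documents supports, and 150 is the planned maximum including the optional Part C.

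**Conclusion.** The inconsistency is real, unexplained and worth correcting, because it decides which data enter primary safety summaries. The defect lies mainly in the protocol: its 14-day limit is up to 2 days too short for its own follow-up visit, and its 14-day collection rule disagrees with its own schedule. The SAP's defect is that it does not declare the departure or state the shorter collection period for non-serious events.

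The size cannot be fixed from the documents. The tables differ only if data fall 15 or more days after the last dose, and anywhere from 0 to 100% of follow-up visits could do so. The 12.5 points are the effect of one subject in one active cohort, not a forecast. The conclusion rests on reading 8.6 literally and on taking the protocol text at hand as the one on which the SAP says it is based.

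**What to change.** Use one analysis window in both documents that covers the whole follow-up visit and keeps later safety data.

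1. Keep the SAP's 30-day upper bound. Align protocol 8.6 to it, or state in the SAP (or in the study report, where the SAP says later changes are documented) that 30 days replaces the 14 days of 8.6.
2. Change protocol 7.3.1.1 so that all adverse events are collected through the follow-up visit.
3. Footnote the treatment-emergent tables: non-serious events were collected through the follow-up visit, serious events and deaths through 30 days.
4. If another window is chosen, change SAP 3.4.1, 7.1.6.1, 7.2, 7.2.2 and 7.2.2.1 together.

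A cut at 16 days for laboratory tests, vital signs and ECGs would fit the visit but is not advisable. It would exclude late follow-up visits. It would also exclude repeat tests that protocol 6.7 and 6.9 allow and that the SAP now keeps for treatment-emergent laboratory abnormalities and for maximum and minimum values.

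Cost: a short protocol amendment, which needs documented ethics approval (protocol 9.1.3 and 9.2.1), a sentence and footnotes in the SAP, and up to 2 more days of adverse event recording at a visit that already takes place. Declaring the departure in the SAP alone settles the analysis window without an amendment, but leaves 7.3.1.1 in conflict with the schedule.
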